# Pedicle screw placement accuracy in robot-assisted versus image-guided freehand surgery of thoraco-lumbar spine (ROBARTHRODESE): study protocol for a single-centre randomized controlled trial

**DOI:** 10.1186/s13063-024-07908-1

**Published:** 2024-02-03

**Keywords:** Pedicle screw placement accuracy, Thoraco-lumbar, Robotic surgery, Freehand surgery, Spinal arthrodesis, Mazor X Stealth

## Abstract

**Background:**

Robotic spinal surgery may result in better pedicle screw placement accuracy, and reduction in radiation exposure and length of stay, compared to freehand surgery. The purpose of this randomized controlled trial (RCT) is to compare screw placement accuracy of robot-assisted surgery with integrated 3D computer-assisted navigation versus freehand surgery with 2D fluoroscopy for arthrodesis of the thoraco-lumbar spine.

**Methods:**

This is a single-centre evaluator-blinded RCT with a 1:1 allocation ratio. Participants (*n* = 300) will be randomized into two groups, robot-assisted (Mazor X Stealth Edition) versus freehand, after stratification based on the planned number of pedicle screws needed for surgery. The primary outcome is the proportion of pedicle screws placed with grade A accuracy (Gertzbein-Robbins classification) on postoperative computed tomography images. The secondary outcomes are intervention time, operation room occupancy time, length of stay, estimated blood loss, surgeon’s radiation exposure, screw fracture/loosening, superior-level facet joint violation, complication rate, reoperation rate on the same level or one level above, functional and clinical outcomes (Oswestry Disability Index, pain, Hospital Anxiety and Depression Scale, sensory and motor status) and cost-utility analysis.

**Discussion:**

This RCT will provide insight into whether robot-assisted surgery with the newest generation spinal robot yields better pedicle screw placement accuracy than freehand surgery. Potential benefits of robot-assisted surgery include lower complication and revision rates, shorter length of stay, lower radiation exposure and reduction of economic cost of the overall care.

**Trial registration:**

ClinicalTrials.gov NCT05553028. Registered on September 23, 2022

## Introduction

### Background and rationale {6a}

There are many indications for thoracolumbar spinal arthrodesis, including deformities (scoliosis, kyphosis), spondylolisthesis, discopathy and spinal instability. Posterior arthrodesis with pedicle screw and rod placement has established itself as the reference technique since the 1980s. The accuracy of this surgical technique was improved by 2D fluoroscopy and then by 3D computer-assisted navigation (CAN), which made it possible to reduce extra-pedicular placement of screws and subsequent complications [1]. Furthermore, in the 2000s, spinal surgical robots were introduced, and these have evolved over the last decades to allow pre- and intraoperative planning (implant selection, optimal trajectory), robotic guidance and real-time 3D navigation [2] thanks to integrating CAN systems within the robotic platform.

Compared to freehand surgery, robotic surgery may result in better pedicle screw placement accuracy [3–5], reduction in intraoperative irradiation [4] and reduction in the length of stay (LOS) [4]. A meta-analysis by Staartjes et al. [6] revealed significantly fewer revisions for screw malposition following thoracolumbar arthrodesis using robotic or CAN guidance compared to freehand surgery, which may imply an association between pedicle screw placement accuracy and revision rates. However, there are few randomized controlled trials (RCT) that have assessed pedicle screw placement accuracy of the newest generation of spinal robots with integrated CAN.

Pedicle screw placement accuracy is an objective outcome measure that can be assessed immediately following surgery and, unlike patient-reported outcomes, does not depend on patient expectations, co-morbidities or follow-up rates. Pedicle screw placement is also one of the most frequently reported outcomes of spinal arthrodesis and facilitates comparisons of surgical methods across the literature.

### Objectives {7}

The objectives are to compare pedicle screw placement accuracy on computed tomography (CT) images of robot-assisted surgery with integrated CAN versus conventional freehand surgery with 2D-fluoroscopy in patients requiring arthrodesis of the thoracic and/or lumbar spine and to compare intervention time, operation room (OR) occupancy time, LOS, estimated blood loss (EBL), surgeon’s radiation exposure, screw fracture/loosening, superior-level facet joint violation, complication rate, reoperation rate on the same level or one level above, functional and clinical outcomes (Oswestry Disability Index [ODI] [7], pain, hospital anxiety and depression scale [HAD], sensory and motor status) and cost-utility analysis.

### Trial design {8}

This is a single-centre evaluator-blinded RCT in a superiority framework with a 1:1 allocation ratio. There will be eight investigating surgeons, each of them capable of performing either intervention (robot-assisted and conventional). All the surgeons have equal experience performing robot-assisted arthrodesis and at least 5 years of experience performing conventional spine arthrodesis.

## Methods: participants, interventions and outcomes

### Study setting {9}

The study is based in the Hôpital Privé Saint Martin, ELSAN Group, [name], France.

### Eligibility criteria {10}

Three hundred patients undergoing posterior arthrodesis of the thoracic and/or lumbar spine will be enrolled.

The inclusion criteria will be as follows:Men and women aged over 18 years,Any indication requiring arthrodesis of the thoracic and/or lumbar spine,Signature of informed consent prior to any study-related procedures,Ability to answer questionnaires and to communicate freely in French,Negative urinary pregnancy test,Affiliation to social security scheme.

The exclusion criteria will be as follows:Psychological disorders,Dependence on analgesics,Chronic infection,History of instrumented thoraco-lumbar surgery,Adult under guardianship, curatorship or other legal protection, deprived of liberty by judicial or administrative decision,Body mass index (BMI) greater than or equal to 40 kg/m^2^Pregnant, postpartum, or breastfeeding women,Participation in another clinical trial.

### Who will take informed consent? {26a}

Participants in the study will sign the written informed consent which will be collected by the investigating surgeon, in accordance with the rules of Good Clinical Practice for biomedical research (Journal Officiel de la République Française n° 0277, decision of November 24, 2006, article 4.8.3).

### Additional consent provisions for collection and use of participant data and biological specimens {26b}

Not applicable.

### Interventions

#### Explanation for the choice of comparators {6b}

Patients will be randomized into two groups, robot-assisted versus conventional, with a 1:1 allocation after initial stratification based on the planned number of pedicle screws needed for surgery, with short-segment fusion comprising four to six screws (two to three vertebrae) and long-segment fusion comprising at least eight screws (more than three vertebrae).

The robot-assisted group will undergo posterior thoracic and/or lumbar arthrodesis using a new-generation surgical robot with integrated real-time 3D navigation (Mazor X Stealth Edition). The conventional group will undergo posterior thoracic and/or lumbar arthrodesis using the freehand surgical technique with 2D fluoroscopy.

#### Intervention description {11a}

Patients will undergo spinal arthrodesis with a pedicle screw placement by posterior approach under general anaesthesia. The robot-assisted group will be operated using a spinal robot with integrated real-time 3D navigation (Mazor X Stealth Edition). All patients in the robot-assisted group will require a CT scan as part of preoperative assessment, to be used for surgical planning and intraoperative navigation. The conventional group will be operated using the freehand surgical technique with 2D fluoroscopy. Surgical access will be open or minimally invasive, depending on the investigating surgeon’s preference and the indication for surgery. Interbody fusion will be performed in selected cases, depending on the indication for surgery.

#### Criteria for discontinuing or modifying allocated interventions {11b}

The investigating surgeon may temporarily or permanently interrupt a patient’s participation in the study for any reason that would serve the best interests of the patient, in particular, in the case of a serious adverse event (SAE). These patients will no longer be monitored under this protocol but will continue to receive the best care possible given their state of health and the current state of knowledge. For all early study withdrawals, the investigating surgeon must document the reasons with as much detail as possible. The study may be interrupted prematurely in the event of the occurrence of unexpected adverse events (UAE). Similarly, unforeseen events or new information regarding medical strategies may lead the sponsor (Hôpital Privé Saint Martin ELSAN) to terminate the study prematurely. Modifications should be documented by the investigating surgeon. Only dropouts result in the discontinuation of follow-up. Even in the event of a deviation from the protocol, the follow-up of the participant must be carried out until the end specified in the protocol.

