#### Plans to promote participant retention and complete follow-up {18b}

The data for the primary outcome (pedicle screw placement accuracy) will be collected on postoperative day 1, so the risk of missing data is small. For the analysis on the ITT dataset, if the evaluation of the placement of a screw is missing, it will be considered that the screw is not correctly placed. If the evaluation of all screws is missing for one patient, the patient will not be analysed, although the patient will still be included in the initial cohort. All the other data are considered secondary outcomes; the missing data will be reported as such in the final analysis. Outcomes will be collected for all the patients regardless of possible protocol deviations or crossovers between treatment arms.

If a patient withdraws prematurely from the study, they will not be replaced, and reasons for patient withdrawal must be documented. For patients lost to follow-up, attempts to contact the patient must be made and documented. No further outcomes will be collected from the patients who discontinue participation in the study.

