## Statistical methods

### Statistical methods for primary and secondary outcomes {20a}

The quantitative variables will be described by the number of values entered, the number of missing data, the mean, the standard deviation, the median, the 1st and 3rd quartiles, the minimum and the maximum. The qualitative variables will be described by the number of values entered, the number of missing data, the frequency, the percentage of each modality and the 95% confidence interval (CI) of each modality, if relevant. The type I error (*α*) is set at 5% with a two-tailed analysis for the entire study. No management of multiplicity will be carried out. The secondary outcomes will be analysed on an exploratory basis. The primary outcome (proportion of grade A placed screws according to Gertzbein-Robbins classification on postoperative day 1) will be described by group (robot-assisted vs. conventional surgery) and compared using a marginal logistic model (taking into account screw clusters in the same patient) including the group and the randomization stratification factor (long-segment fusion vs. short-segment fusion). The results of the marginal logistic model will be interpreted in terms of adjusted odds ratio (aOR) accompanied by the 95% CI. Intervention time, OR occupancy time, LOS, EBL and surgeon’s intraoperative radiation exposure will be described by group (robot-assisted vs. conventional surgery) and compared using an analysis of variance (ANOVA) including the group and the randomization stratification factor (long-segment fusion vs. short-segment fusion). Radiological stability (signs of screw fracture/loosening), superior-level facet joint violation, complication and reoperation rates will be compared using logistic regression including the group and the stratification factor of the randomization (long-segment fusion vs. short-segment fusion). Functional outcomes (ODI, pain, HAD) will be compared using an analysis of covariance (ANCOVA) including the group, the score at inclusion and the randomization stratification factor (long-segment fusion vs. short-segment fusion); this analysis will be carried out at each evaluation time (3-, 12- and 24-month follow-up). The evaluation of sensory status and motor status will be compared using a Cochran-Mantel-Haenszel test including the group and the stratification factor of the randomization (long-segment fusion vs. short-segment fusion); this analysis will be carried out at each evaluation time (3-, 12- and 24-month follow-up). The cost-utility analysis will be carried out according to the recommendations of the French National Authority for Health (HAS) [11], based on QALYs (lifespan weighted by health-related quality of life), derived from the EQ5D-5L. All direct medical costs will be measured over 12 months following hospital discharge. The incremental cost-utility ratio (difference in costs divided by the difference in QALYs) between robot-assisted surgery and conventional surgery will be determined at 12 months along with their 95% CIs. All statistical analysis will be performed using the latest version of the SAS software.

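### Outcome collection may stop when the surgeon ends participation after a serious adverse event, causing outcome-related loss in the exploratory secondary outcomes

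*Protocol article*

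**What the plan says.** All references are to the protocol article.

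- **Criteria for discontinuing {11b}.** The surgeon may interrupt participation, temporarily or permanently, when this is in the patient's interest. One situation is singled out: "in particular, in the case of a serious adverse event (SAE". For patients so interrupted, "These patients will no longer be monitored under this protocol", although their clinical care goes on.
- **The same section, further down.** "Only dropouts result in the discontinuation of follow-up". After a protocol deviation, "the follow-up of the participant must be carried out until the end specified in the protocol".
- **Retention and follow-up {18b}.** "Outcomes will be collected for all the patients regardless of possible protocol deviations or crossovers between treatment arms", but also "No further outcomes will be collected from the patients who discontinue participation in the study". For secondary outcomes, "the missing data will be reported as such in the final analysis".
- **Outcomes {12} and Table 3 {13}.** Complications and reoperations are counted to 24 months. CT for screw fracture or loosening is at 12 and 24 months. ODI, pain and HAD are at 3, 12 and 24 months. EQ-5D-5L is at inclusion, 3 and 12 months.
- **Statistical methods {20a}.** "complication and reoperation rates will be compared using logistic regression including the group" and the stratification factor. Secondary outcomes are exploratory. {18a} places them on the intention-to-treat set of operated patients.
- **Blinding {17a}.** Only the radiologists who grade screw placement are blinded. The surgeon is not.

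**The concern.** The allocated treatment is a single operation ({11a}). Once it is done, ending participation withdraws no continuing study treatment. What it mainly ends is data collection.

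The event named as the example for ending it is closely tied to the outcomes. The surgery-related SAEs that {22} expects include infection, neurological deficit, vessel injury, mechanical failure, implant loosening, screw fracture and malposition. These overlap the complication types in {12}. {22} also treats any adverse event that leads to or prolongs a hospital stay as an SAE, so most events on the way to a reoperation would qualify. A patient removed after such an event is more likely than others to have a further complication, a reoperation, a poor functional score or high costs, and none of that would be seen.

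The person who decides on removal knows the arm, so removal could differ between arms. The trial has no data monitoring committee ({21a}) and no interim analysis ({21b}), and its abstract names lower complication and revision rates among the hoped-for benefits. Comparative evidence on these therefore rests on the 24-month follow-up.

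**Working it through.** **1. The rules side by side**

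| Situation | Rule | Data afterwards |
|---|---|---|
| Protocol deviation | {11b}, {18b} | Continue to the planned end |
| Crossover | {18b} | Continue |
| Dropout (not defined) | {11b} | Stop |
| Surgeon interrupts, for example after an SAE | {11b} | No longer monitored |
| Patient discontinues participation | {18b} | Stop |

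Two points do not fit together.

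- If a surgeon's interruption is not a dropout, row 4 contradicts the rule that only dropouts end follow-up. If it is a dropout, the sentences agree, but the word only then restricts little and the loss after an SAE remains.
- {11b} allows a temporary interruption, yet the consequence it states is that monitoring ends, with no provision for resuming it.

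**2. What is lost and what is kept**

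- Kept: the triggering event, because {22} requires each adverse event to be assessed and recorded and Table 3 collects complications and adverse events from surgery onward. Also kept is the day-1 CT, unless removal comes before it.
- Lost: later complications and reoperations, CT at 12 and 24 months, later ODI, pain and HAD, EQ-5D-5L up to 12 months, and the rest of the 12-month costs.

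**3. The plan's own allowance**

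The sample size reproduces and is not in question. With 88% against 95%, two-sided 5% and 90% power, the unpooled formula gives 328.3 screws per group. The design effect is 1 + (5 − 1) × 0.3 = 2.2, and 328.3 × 2.2 = 722.3. At 5 screws per patient this rounds up to 145 patients, or 725 screws, as stated. The 5% allowance covers only patients randomized but not operated on, leaving 150 × 0.95 = 142.5, or about 142 per arm. Nothing is allowed for later loss.

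**4. Direction and possible size (all rates assumed; the documents give none)**

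Let *r* be the true 24-month reoperation rate. Let *w* be the share of would-be reoperated patients removed before the reoperation is counted.

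- Removed patients left out of the denominator: observed rate = *r*(1 − *w*) / (1 − *rw*).
- Removed patients kept as event-free: observed rate = *r*(1 − *w*).

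True rates of 10% and 5%, same *w* in both arms, removed patients left out:

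| *w* | Observed | Difference (points) | Ratio |
|---|---|---|---|
| 0 | 10.0% vs 5.0% | 5.0 | 2.00 |
| 25% | 7.7% vs 3.8% | 3.9 | 2.03 |
| 50% | 5.3% vs 2.6% | 2.7 | 2.05 |
| 75% | 2.7% vs 1.3% | 1.4 | 2.08 |

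Example for *w* = 25%: 0.10 × 0.75 / (1 − 0.025) = 0.0769, and 0.05 × 0.75 / (1 − 0.0125) = 0.0380. With removed patients kept as event-free, the difference is 3.75, 2.5 or 1.25 points and the ratio stays at 2.0.

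True rate of 10% in both arms, different *w* by arm, removed patients left out:

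- 25% vs 50%: 7.7% vs 5.3%, a false difference of 2.4 points.
- 0 vs 50%: 10.0% vs 5.3%, a false difference of 4.7 points.

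Equal removal therefore understates the absolute rates and the risk difference but barely moves the ratio. Unequal removal can create or hide a difference.

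**The case against.** Several objections carry weight.

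- **Removal is discretionary.** A reader might infer that every patient with an SAE leaves the trial, so that the patients who generate the complication and reoperation outcomes disappear. {11b} does not say that. It says the surgeon may interrupt, gives an SAE as an example and allows a temporary interruption. No frequency is given.
- **The triggering event is recorded.** A patient removed because of an infection or an implant failure already has a complication on file, and a reoperation that prompts removal would be on file too. The loss is confined to what comes later.
- **The contradiction depends on a word.** If dropout covers surgeon-initiated withdrawal, {11b} and {18b} can be read together. A reader might infer two flatly opposed rules, but the text supports only an undefined term and an awkward fit.
- **A biased relative effect is not a given.** A reader might infer that the risk ratio must be distorted. With equal removal it hardly changes. Distortion needs removal to differ by arm, which the unblinded decision makes possible but which no passage shows.
- **The analysis method is not the fault.** Detailed handling of missing secondary data is commonly left to the analysis plan, which is not at hand. Moving to time-to-event methods would not help by itself, since censoring a patient removed after an SAE is itself informative.

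All of this limits the point without removing it. The rule decides what is collected, and no analysis plan can recover outcomes that were never recorded.

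**Conclusion.** The point holds in a limited form. Followed as written, {11b} and {18b} allow outcome collection to end at the discretion of an unblinded surgeon, with an SAE as the named example. The resulting loss is related to the later secondary outcomes. Their absolute event rates would be understated, and the comparison between arms would be distorted if removal differed by arm. The wording also leaves staff unsure when follow-up ends.

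The size cannot be stated, because the documents give neither event rates nor removal rates. The figures worked out above rest on assumed rates and show direction and range only. Day-1 screw accuracy and the sample size are largely or wholly unaffected, and every affected outcome is secondary and exploratory. Severity is moderate, and the change is a cheap improvement.

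**What to change.** Reconcile {11b} and {18b} in the protocol:

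1. Separate the end of participation in study procedures from the end of outcome collection.
2. State that an SAE, a protocol deviation or a crossover does not by itself end collection of the scheduled outcomes to 24 months. At minimum this covers complications, reoperations and the questionnaires on their existing schedule, with CT where the patient still attends.
3. State that only the patient's withdrawal of consent ends outcome collection.
4. Define dropout, and say how collection continues during and after a temporary interruption.

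How an SAE is managed clinically, and whether a surgeon interrupts study procedures, is outside this point and stays as it is.

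The cost is protocol wording plus some extra follow-up effort for patients who would otherwise have been removed. The visits are already in Table 3, and the 300 patients do not change.

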#### Strategies to improve adherence to interventions {11c}

To improve adherence to interventions, preoperative CTs will be easily accessible for patients allocated to the robot-assisted group, and the necessary surgical equipment will be available at all times for both groups.

#### Relevant concomitant care permitted or prohibited during the trial {11d}

There is no specific concomitant care administered nor prohibited during the trial.

#### Provisions for post-trial care {30}

There is no anticipated harm or compensation for trial participation. Participation in the study will stop 24 months after arthrodesis; patients will undergo routine follow-up.

### Outcomes {12}

The primary outcome of this study will be the rate of pedicle screws placed with grade A accuracy according to Gertzbein-Robbins classification (Table 1) in the robot-assisted versus conventional groups. The evaluation of the placement of the screws will be based on CT images from postoperative day 1 and will be carried out by two radiologists independent to the surgical team, blinded to the technique used for screw placement. In case of disagreement between the two evaluators, a 3rd evaluator will be requested.

**Table 1 Tab1:** Gertzbein-Robbins classification of pedicle screw placement

Grade A	fully intrapedicular position without breach of the pedicle cortex
Grade B	<2 mm cortical breach
Grade C	2-4 mm cortical breach
Grade D	4-6 mm cortical breach
Grade E	exceeding the pedicle cortex <6 mm or is outside of the pedicle

The secondary outcomes of the study will be as follows:Intervention time (min)OR occupancy time (min)LOS (days)EBL (volume of the suction jar at the end of the intervention in ml)Surgeon’s intraoperative radiation exposure (a dosimeter placed in contact with the surgeon’s clothing, in cGy/cm^2^)Signs of screw fracture/loosening (CT at 12 and 24 months postoperatively)Superior-level facet joint violation according to Babu-Mehta classification (Table 2; CT on postoperative day 1)Types of complications (neurologic, infectious, vascular, general, late and early mechanical complications) and complication rate at 24 months postoperativelyReoperation rate on the same instrumented level or one level above at 24 months postoperativelyFunctional and clinical outcomes at 3, 12 and 24 months postoperatively (pain on visual analogue scale [VAS; 0, best; 10, worst], ODI [0, best; 100, worst], HAD scale [0, best; 21, worst], sensory status with 3-point scale [0, absent sensation; 2, normal sensation], motor status with Medical Research Council’s [MRC] scale for muscle strength [0, no contraction; 5 full muscle strength])Cost-utility analysis based on medical costs and quality of life (QoL) evaluation (quality-adjusted life years [QALYs] derived from EuroQol [EQ-5D-5L questionnaire) at 12 months postoperatively

**Table 2 Tab2:** Babu-Mehta classification of facet joint violation

Grade 0	Screw not in facet
Grade 1	Screw in lateral facet but not in facet articulation
Grade 2	Penetration of facet articulation
Grade 3	Screw travels within facet articulation

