### Assignment of interventions: blinding

#### Who will be blinded {17a}

This is an evaluator-blinded study, in which both the investigating surgeon and participant know which treatment is being administered. The only people blinded to the treatment arm are the two radiologists evaluating pedicle screw placement on postoperative CT images.

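### Estimated blood loss is defined as the whole suction-jar volume, so as written it measures total aspirated fluid and not blood alone

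*Protocol article*

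**What the plan says.** Outcomes {12} lists estimated blood loss among the secondary outcomes and defines it as "EBL (volume of the suction jar at the end of the intervention in ml". The abstract and Objectives {7} also name it as an outcome.

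Plans for assessment and collection of outcomes {18a} lists EBL as an e-CRF item, with no further definition and no companion field for other fluids. Irrigation, swabs and cell salvage are not mentioned anywhere in the article.

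Statistical methods {20a} groups it with other continuous outcomes ("Intervention time, OR occupancy time, LOS, EBL" and surgeon's radiation exposure), to be "compared using an analysis of variance (ANOVA) including the group and the randomization stratification factor", that factor being long- versus short-segment fusion. The same section says: "The secondary outcomes will be analysed on an exploratory basis".

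Two design features bear on what may enter the jar. Intervention description {11a} says: "Surgical access will be open or minimally invasive, depending on the investigating surgeon’s preference and the indication for surgery". Who will be blinded {17a} says: "The only people blinded to the treatment arm are the two radiologists evaluating pedicle screw placement on postoperative CT images".

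**The concern.** A suction jar collects whatever is aspirated from the field. If that includes wash fluid, the jar volume is blood plus irrigation, and the stated rule reports the sum as blood loss. Blood that never reaches the jar, for example on swabs, is not counted, and this error runs in the opposite direction. The result would still be published in millilitres as blood loss.

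There are two consequences, and they differ in standing. The first needs only that irrigation reaches the jar and varies between patients: the level is raised and the comparison loses precision. The second needs more. If irrigation volume differed on average between the robot-assisted and freehand arms, that difference would be reported as a difference in bleeding. Randomization would not remove it, because irrigation happens after allocation and could depend on technique or access.

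**Working it through.** **Is there a figure to reproduce?** No. The sample-size section concerns the primary outcome only. No SD, expected difference or power is given for EBL.

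**Reading the sections together.** {12} gives a complete operational definition (the jar, end of operation, ml). {18a} and {20a} add no deduction, no irrigation field and no irrigation covariate. The definition in {12} therefore stands as stated.

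**Inputs from the article.** 150 patients randomized per group, 5% of whom are expected not to be operated: 150 × 0.95 = 142.5, taken as 142 per arm.

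**Inputs assumed.** Blood-loss SD 300 ml; irrigation SD 150 to 300 ml, independent of blood loss. Since the ANOVA adjusts for fusion length, read these as SDs within stratum.

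**Loss of precision when irrigation is equal on average in both arms.**

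Jar SD = √(SD_blood² + SD_irrigation²); SE of the difference = SD × √(2/142) = SD × 0.1187.

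| Irrigation SD (ml) | Jar SD (ml) | SE of difference (ml) | Increase in SE |
|---|---|---|---|
| 0 | 300 | 35.6 | – |
| 150 | √(300² + 150²) = 335 | 39.8 | 335/300 = 1.12, so 12% |
| 300 | √(300² + 300²) = 424 | about 50 | 424/300 = 1.41, so 41% |

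The last row is the extreme of the assumed range: irrigation would have to vary as much as bleeding itself.

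**If irrigation differed between arms (conditional; not shown in the article).** A mean difference d in the irrigation reaching the jar shifts the reported EBL difference by exactly d. With no true difference in bleeding, the chance of p < 0.05 is 1 − Φ(1.96 − d/SE) + Φ(−1.96 − d/SE), where the SE uses the total jar SD:

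| Assumed jar SD (ml) | SE (ml) | d = 50 ml | d = 100 ml |
|---|---|---|---|
| 200 | 23.7 | 56% | 99% |
| 300 | 35.6 | 29% | 80% |
| 400 | 47.5 | 18% | 56% |

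Example: SD 300 and d = 100 give d/SE = 100/35.6 = 2.81, and 1 − Φ(1.96 − 2.81) = 0.80.

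The second table shows how sensitive the comparison would be to such a difference. It does not estimate one.

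**The case against.** The strongest reply has four parts.

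*The premise is not in the article.* Nothing says that wash fluid enters the jar at this centre, or that the volume is read without netting it off, and the unpublished full protocol might contain a netting rule. This stands in part: the premise is an assumption from ordinary operating-room practice and must be labelled so. It does not dispose of the point, because the article gives a complete definition rather than leaving one open, and anyone following it would record the whole jar.

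*The outcome is only an estimate.* The jar does contain the aspirated blood. A reader might infer that the outcome does not measure blood loss at all; the text does not support that. It supports a crude proxy with too specific a name.

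*Bias between arms is conjecture.* A reader might also infer that the EBL comparison is systematically biased, since unblinded surgeons choose the access. The article does not show this. Trial design {8} says each of the eight surgeons can perform either technique, so personal habit is not tied to an arm. Fusion length is both stratified and modelled. Access depends on indication as well as preference, and randomization balances indication on average. If access did differ by arm, true bleeding could differ too. With equal mean irrigation, the group difference in jar volume is not distorted by irrigation and only noise is added. This objection stands.

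*Nothing important depends on it.* The outcome is exploratory, and no sample size or primary conclusion rests on it. This also stands and limits the severity.

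**Conclusion.** The definition needs correcting: total aspirated volume is labelled as blood loss. This follows from the text together with one ordinary assumption, that irrigation is aspirated into the jar. The effect is a raised level and lost precision, with a standard error 12–41% wider under assumed SDs that have no source in the article. Distortion of the group difference is possible if irrigation varies by technique or access, but it has not been demonstrated and should not be claimed. Severity is minor: the primary outcome and sample size are untouched.

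**What to change.** 1. Record the irrigation volume delivered to the field on the e-CRF for each operation.
2. Define EBL as suction-jar volume minus that irrigation volume.
3. State how blood outside the jar is counted: swabs, and any cell-salvage volume if salvage is used.
4. For operations without a recorded irrigation volume, report the outcome as suction volume and not as blood loss, and do not pool the two measures under one name. Recruitment started on 26/12/2022 with an estimated end of 26/12/2024, so this may apply to many patients.
5. If the full protocol already nets off irrigation, say so in the definition.

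The cost is one or two numbers per operation and a reworded outcome; relabelling alone costs nothing. Two limits remain. Irrigation that is not re-aspirated is still subtracted, so the corrected value will be somewhat low. And unless swabs are counted in some stated way, blood outside the jar is still missed.
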